#### Other measures:

All-cause mortality: WHO guidelines will be used for collecting the verbal autopsy for any deaths reported during the study.(63)

#### Data Management:

Data will be captured and stored via REDCap—a secure, HIPAA-compliant, web-based application designed for use in research studies. REDCap features for secure collection and storage of sensitive data include: 1) SSL encryption of data; 2) ability to collect data in real-time to minimize data entry errors; 3) ability to build in real-time data entry validation; and 4) built-in audit trails. Research staff will directly enter data on encrypted laptops/tablets during interactions with patients, except for TLFB interview for alcohol, which will be collected on paper and then double entered into REDCap by study staff. REDCap has ability to check accuracy of double-entered data. Participants can directly enter data via tablets, through the REDCap mobile app.

### Retention

Study staff will complete locator information for all enrolled participants so that they can be tracked if they miss a visit. Prior to the follow up visit study staff will receive a list of expected participants for whom visits are scheduled daily. Participants will be provided with an appointment card with the date of their next scheduled visit and contact details of study staff. Additionally, participants will be reminded by phone call before their scheduled visit to maximize retention. All participants will be advised to contact the study staff if they will not be able to come for their scheduled follow-up visits. In the special instances (e.g. personal or social reasons) where participants are unable to visit the study site within the visit window period, the study staff will carry out a home/telephone/virtual visit. The study sites also have home visitors to contact participants in case they are not reachable by phone.

We have scheduled study and intervention visits to correspond with routine patient clinic visits as much as possible to lessen the burden on participants and improve implementation feasibility if/when this intervention is scaled up beyond our trial. Most participants in this population are expected to have cell phones. Thus, we will set up routine phone calls to increase follow-up. Finally, we have an outreach team and mobile vans to conduct home visits for missed research visits as needed.

Maintaining high rates of follow-up in this study is critical for ascertaining study outcomes. We will provide Rs 350 (USD $4.20) per study visit as compensation for loss of daily wages to the participant. As the study procedure will take 2–3 hours, food will be provided to the participant and others who are accompanying persons. Local transportation will also be paid as actuals by public transport.

### Statistical method

#### Aim 1: Intervention effect on alcohol use

All randomized participants will be included in the primary analysis according to the intervention arm to which they were originally assigned, consistent with the intention-to-treat principle. The primary outcome of the trial is the concentration of PEth measured at 6 months post-randomization. PEth will be analysed as a continuous outcome; distributional assumptions will be assessed, and if the PEth values demonstrate substantial right skewness, an appropriate log transformation will be applied prior to analysis. Given the randomized controlled design, baseline characteristics are expected to be balanced across intervention arms. Nevertheless, we will formally evaluate baseline characteristics by summarizing demographic and clinical variables by study arm using descriptive statistics. The primary analysis will use univariable linear regression to estimate the mean difference in PEth between study arms, incorporating random effects for study site and counsellor to account for potential correlation within these units. If imbalances in baseline characteristics are observed, we will conduct sensitivity analyses to evaluate the impact of these imbalances on treatment effect estimates. Adjusted analyses, including prespecified baseline covariates (e.g., age, gender, religion) and psychosocial and clinical covariates (e.g., depression, smoking, diabetes), will be conducted as supportive and sensitivity analyses to improve precision and to assess the robustness of the primary findings. Participants with missing primary outcome data will not be excluded from the analysis. Instead, missing PEth values will be addressed using prespecified methods, including last observation carried forward and/or multiple imputation, as appropriate. Sensitivity analyses will be performed to compare results across these approaches to evaluate the impact of missing data assumptions on the study conclusions. We will also assess whether the intervention effect varies by treatment intensity (dose), operationalized as the number of intervention sessions attended and the number of booster sessions received. Because factors influencing intervention adherence may also be associated with the outcome, analyses restricted to specific compliance patterns may introduce selection bias. To address this potential bias, we will use inverse probability of censoring weights estimated conditional on baseline and time-varying covariates.

Secondary alcohol-related outcomes include self-reported alcohol consumption assessed using the 30-day TLFB interview. The number of drinking days over the prior 30 days will be analysed as a count outcome, conceptualized as arising from a binomial distribution, Binomial (30, *p*), where *p* represents the proportion of days on which alcohol consumption occurred. The independent effect of the intervention on the proportion of drinking days will be evaluated using adjusted random effects generalized linear models with a logit link function, incorporating random effects for study site and counsellor to account for within group correlation. Differences between intervention arms in the number of self-reported heavy drinking days over the prior 30 days, as measured by the TLFB, will be assessed using multivariable generalized linear random-effects logistic regression models, incorporating random effects for study site and counsellor to account for within group correlation. Intervention effects on other secondary alcohol-related outcomes derived from PEth and AUDIT measures will similarly be evaluated using multivariable random-effects logistic regression models, as appropriate for the outcome distribution. All adverse events (AEs), including serious adverse events (SAEs), and deaths will be monitored and recorded in accordance with the study protocol and established study procedures. AEs and SAEs will be summarized descriptively by study arm using counts and proportions. For comparative analyses between intervention arms, outcomes with binary response distributions will be analysed using multivariable logistic regression models, while count-based AE outcomes will be analysed using multivariable Poisson regression models (or alternative count models if indicated), with appropriate adjustment for clustering and covariates.

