##### Sample size

The effectiveness of the HATHI intervention will be assessed at 6 months using PEth as the primary outcome. A total sample size of 450 participants provides 80% power at a 5% significance level to detect a minimum mean difference of 90 ng/mL between randomized arms. This calculation assumes a mean PEth of 212 ng/mL (SD = 205 ng/mL), as observed in the ongoing HATHI study. Calculations assume a 10% loss to follow-up, and intra-class correlation coefficient of 0.04 to account for site-counsellor clustering.

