##### Randomization procedures: Sequence generation and allocation concealment

Eligible participants will be randomized in a 1:1 ratio upon completion of the baseline evaluation. The study biostatistician, independent of the trial will generate the randomization sequence in permuted blocks with block size 4, and randomization will be stratified by the presence of TB only; HIV only; and TB/HIV co-infection. Allocation will be concealed using sequentially numbered, opaque, sealed envelopes. The study counselor will enroll and assign participants to the interventions

By nature of the interventions being tested, this will be an open-label trial in which neither the subjects, study coordinators, nor interventionists will be blinded to treatment assignment after randomization. However, to decrease potential sources of bias, research assistants, staff abstracting medical records, and data analysts will all be blinded to treatment arm of individual patients.

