### Methods in analysis to handle protocol non-adherence and any statistical methods to handle missing data

The sample size calculation incorporates a 10% allowance for loss to follow-up or missing data at the 6-month primary endpoint to preserve 80% statistical power. Given the high rates of attrition typically observed in alcohol intervention trials, we will assess the mechanism of missingness (missing completely at random, missing at random, missing not at random), acknowledging that this is rarely verifiable in practice. Missing data will be addressed using four approaches: last observation carried forward, worst-case scenario imputation (classifying all missing as heavy drinking & using upper limit of PEth detection), multiple imputation with chained equations, and full information maximum likelihood estimation. Auxiliary variables (baseline alcohol use measures, age, TLFB, AUDIT, etc.) will be included in the latter two methods, and sensitivity analyses will be performed across all approaches to evaluate robustness.

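### No single method is named for missing 6-month PEth in the primary analysis, and the wording lets last observation carried forward supply the primary estimate

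*Protocol article*

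**What the plan says.** The protocol article treats missing primary-outcome data in two places.

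- **Statistical method, Aim 1.** All randomized participants enter the primary analysis, and those without a 6-month PEth are not excluded. Instead, "missing PEth values will be addressed using prespecified methods, including last observation carried forward and/or multiple imputation, as appropriate". Results are then to be compared across approaches in sensitivity analyses.
- **Section on protocol non-adherence and missing data.** "Missing data will be addressed using four approaches: last observation carried forward" opens a list that continues with "worst-case scenario imputation (classifying all missing as heavy drinking & using upper limit of PEth detection"), multiple imputation with chained equations, and full information maximum likelihood. Auxiliary variables are promised for the last two; the examples given are baseline alcohol measures, age, TLFB and AUDIT. Sensitivity analyses run across all four. The section also remarks that attrition is typically high in alcohol trials.

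Neither place says which method yields the primary estimate, or what decides appropriateness. The upper limit of detection is not given. Tables 2 and 3 schedule PEth at months 3, 6 and 12, and Table 3 also at baseline. The data-collection section marks month 3 as the end of the four-session intervention.

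**The concern.** Because nobody with a missing outcome is dropped, the missing-data method is part of the primary estimate. The methods are called prespecified but worded as an open choice, and the second list is longer than the first. Two of the four are single imputations that can move the answer.

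Carry-forward fixes a dropout at the value measured when the core sessions end, so later relapse is not seen. Without a month-3 sample it falls back to baseline. The upper-limit rule puts an extreme value into a continuous outcome for everyone missing, so the result depends heavily on how many are missing in each arm. At stake is whether the headline PEth difference follows from a rule fixed in advance or from a choice between methods that can disagree.

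**Working it through.** **Inputs from the Sample size section.** "a minimum mean difference of 90 ng/mL between randomized arms"; "This calculation assumes a mean PEth of 212 ng/mL (SD = 205 ng/mL"); "Calculations assume a 10% loss to follow-up, and intra-class correlation coefficient of 0.04 to account for site-counsellor clustering". Allocation is 1:1. Taking 212 as the control mean, the implied intervention mean is 212 − 90 = 122.

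**The plan's own figure.** Two-sided 5%, 80% power: n per arm = 2 × (1.960 + 0.842)² × 205² / 90² = 81.4, so 82, or 164 in total. With 10% loss, 164 / 0.9 = 182.2, so 183. Reaching 450 needs a design effect of 405 / 164 = 2.47, which at an ICC of 0.04 means a cluster size of about 38. The article states no cluster size, so 450 is compatible with its inputs but cannot be confirmed. That is a separate matter; only the 90, 212, 205 and 10% are used below.

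**Carry-forward, 10% missing in each arm.**

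1. *Month-3 value carried; intervention-arm dropouts rise 60 to 100 ng/mL after month 3, control dropouts do not (assumed).* Bias = 0.10 × 60 = 6 to 0.10 × 100 = 10 ng/mL in favour of the intervention.
2. *Baseline mean of 212 carried in both arms; the true difference is 90 in dropouts too (assumed).* Control: 0.9 × 212 + 0.1 × 212 = 212. Intervention: 0.9 × 122 + 0.1 × 212 = 131. Difference = 81 instead of 90. With 5% missing in control and 15% in intervention it is 76.5; reversed, 85.5.

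The bias can go either way, depending on which visit is carried and what dropouts really did.

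**Upper-limit rule, raw scale.** Let U be the upper limit (assumed 1000 or 2000 ng/mL). With equal true means of 212 and missingness 5 points higher in one arm, the spurious difference is 0.05 × (U − 212):

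| U assumed (ng/mL) | Spurious difference (ng/mL) | Share of the 90 target |
|---|---|---|
| 1000 | 39.4 | 44% |
| 2000 | 89.4 | 99% |

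With 10% missing in both arms the SD becomes √(0.9 × 205² + 0.09 × (U − 212)²) = 306 or 571, against 205.

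Now take a true difference of 90:

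| Missing, control / intervention | U = 1000 | U = 2000 |
|---|---|---|
| 10% / 10% | 81 | 81 |
| 5% / 15% | −2 | −102 |
| 15% / 5% | 164 | 264 |

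The last row is why the rule is not reliably conservative: it exaggerates benefit when more control participants are missing.

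**Upper-limit rule, log scale.** The article would log-transform if PEth is substantially right-skewed. Assuming lognormal PEth with mean 212 and SD 205, the log variance is ln(1 + (205/212)²) = 0.660 and the log mean is ln 212 − 0.330 = 5.027. The target is ln(212/122) = 0.553. The 5-point gap shifts the result by 0.05 × (ln U − 5.027):

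- U = 1000: 0.094, or 17% of the target.
- U = 2000: 0.129, or 23% of the target.

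**The case against.** Several defences are fair.

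- **The two sections do not strictly contradict each other.** The Aim 1 list is introduced as non-exhaustive, so the later list can be read as completing it. That stands. What remains is that neither says which method is primary.
- **Ranking methods is often left to an analysis plan, which is not shown.** True in general. Here, though, the article does address the point, and does so by permitting carry-forward in the primary analysis. That is a choice on the page, not an omitted detail.
- **Analysts are blinded and all approaches will be compared.** This limits selective choice. It does not define the primary estimate, or say what to conclude if the approaches disagree.
- **The upper-limit rule is a stress test.** It appears only in the later section, not in the Aim 1 primary-analysis text, and extreme imputations are meant to depend on who is missing. That stands. The remaining criticism is that a stress test for a continuous outcome should have a predictable direction and a stated value, and this one has neither.

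Two stronger readings should be resisted. A reader might infer that the primary result is already biased. The documents do not support this: chained-equations imputation and likelihood estimation, both valid under missing at random, are planned, and bias arises only if a single imputation supplies the primary estimate.

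A reader might also infer that carry-forward inflates the type I error because 450 rather than 405 people are counted. That does not follow: each carried value is a real, independent measurement on that person. Under the null with equal missingness (lognormal PEth, month-3 to month-6 correlation 0, 0.5 or 0.8, clustering ignored), a simulated two-sample test rejects in about 4.5% to 5% of trials at both 10% and 20% missing. The problem with carry-forward is bias in the estimate.

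**Conclusion.** The concern holds in a limited form: as written, the method behind the primary estimate is not determined, and carry-forward is an allowed answer.

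Its effect is modest at the planned 10% loss, roughly 6 to 10 ng/mL on a 90 ng/mL target, in a direction that depends on which visit is carried. Those figures rest on assumed dropout behaviour and would grow with attrition.

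The upper-limit rule can have a much larger effect on the raw scale (39 to 89 ng/mL for a 5-point imbalance) and a smaller one on the log scale (17% to 23% of target). Both ranges rest on an assumed limit and imbalance, and the log figures also on a lognormal shape. Its bearing is on how the sensitivity analysis is read, unless it is chosen as primary.

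This is a should-fix point.

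**What to change.** 1. **Name one primary method valid under missing at random:** multiple imputation by chained equations within arm, or a likelihood-based repeated-measures model. Both are in line with methods already planned. State that it uses baseline and month-3 PEth, disease cohort, site, TLFB and AUDIT, on the same scale as the analysis. Month-3 PEth is not named in the current auxiliary list.
2. **Take carry-forward out of the primary analysis.** Keep it, if at all, as a labelled sensitivity analysis.
3. **For continuous PEth, replace the upper-limit rule with delta-adjusted multiple imputation** on the analysis scale, varied by arm to a tipping point, as the missing-not-at-random sensitivity analysis. Counting missing as heavy drinking can stay for the binary PEth thresholds.
4. **Report deaths by arm beside the primary result.** The upper-limit rule as worded covers all missing values and makes no exception for deaths.
5. **Use the same text in both sections,** without the open and/or wording.

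The cost is protocol or analysis-plan wording and a little extra analysis. No new data are needed, since month-3 PEth is already scheduled. The change should be made before outcomes are compared by arm.

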###### TLFB:

Using structured interview prompts, the TLFB quantifies alcohol use on each day over the last 30 days. TLFB yields detailed quantity/frequency data including number of abstinent days and drinking days, mean number of drinks/drinking day, and number of heavy (binge) drinking days.(44)

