## Discussion

Unhealthy alcohol use is a known risk factor for both HIV and Tuberculosis infection acquisition and for poorer HIV and TB treatment outcomes. HATHI,- **H**ybrid trial for **A**lcohol reduction among people with **T**B and **H**IV in **I**ndia, is to our knowledge one of the first hybrid effectiveness-implementation studies testing the effectiveness of an evidence-based behavioral alcohol reduction intervention integrated into TB and HIV clinical care in India. As such, this study will generate new knowledge that will inform delivery of alcohol counseling among people with TB and HIV in these clinical settings

Strengths to this study include the intentional selection of the hybrid design, that allows for the rigor of a randomized controlled trial and the collection of implementation barriers and facilitators of alcohol intervention integration into these clinical settings. Additional strengths include selection of an evidence-based intervention with core components effective in HIV clinical settings and in Indian primary care clinics that has been culturally adapted for people with HIV and TB in India and rigorous quality and fidelity monitoring of behavioral counseling sessions. Finally, use of an alcohol biomarker, PEth, as our primary outcome will overcome challenges of underreported alcohol use due to social desirability.

Despite these strengths, there have been challenges to trial implementation. Specifically, low self-report of alcohol use on the TLFB interview, in contrast to the AUDIT and PEth was noted, resulting in DSMB recommendation to change the primary outcome from self-report to biomarker. Moreover, enrollment of women in the study has been limited, which is likely attributable to the lower prevalence of alcohol use among women in India and potential under-reporting due to the low social acceptability of alcohol use among women in this context. Finally, we have experienced interruptions in recruitment of people with TB at various timepoints in the study due to lack of TB medication availability resulting in reduced screening (April-June 2024) and a TB health staff strike (February 11, 2024-March 5, 2024, and August 18-September 17, 2024).

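### Drinking days (TLFB, secondary outcome) are modelled as Binomial(30, p) with random effects for site and counsellor only, so person-to-person variation is left out and standard errors are too small by about sqrt(1 + 29·rho).

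*Protocol article*

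**What the plan says.** In the protocol article, Statistical method, Aim 1, the count of self-reported drinking days "will be analysed as a count outcome, conceptualized as arising from a binomial distribution", with 30 trials and a probability p that stands for the share of days with drinking. The arm effect on that share is to be estimated with "adjusted random effects generalized linear models with a logit link function, incorporating random effects for study site and counsellor". The TLFB paragraph under data collection shows where the 30 trials come from: "the TLFB quantifies alcohol use on each day over the last 30 days". All 30 come from one interview with one person.

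The "number of self-reported heavy drinking days over the prior 30 days" is to be compared between arms by random-effects logistic regression with the same two random effects. The text does not say whether that response is days out of 30 or a yes/no indicator.

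The same section does allow a departure from the default model, "or alternative count models if indicated", but only for adverse event counts. Drinking days have no such clause. The Outcomes section lists them as a secondary outcome at months 6 and 12, and Table 2 adds month 3.

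**The concern.** A binomial count has variance 30p(1−p) only if the 30 days are independent given the terms in the model. Those terms are arm, covariates, site and counsellor. None of them represents the difference between one participant and the next within the same clinic and counsellor.

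That difference is likely to be large here. Eligibility starts at an AUDIT score of 8 (men) or 6 (women) and extends to severe alcohol use disorder after psychiatric clearance. The Sample size section gives PEth a mean of 212 and an SD of 205 ng/mL. The Discussion reports "low self-report of alcohol use on the TLFB interview", which points to many low or zero counts beside some high ones.

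If this spread is not modelled, the model claims more information than the trial has. Its intervals are too narrow and its tests reject too often. A chance difference in self-reported drinking could then be read as support for the intervention, in an open-label trial where one arm has been counselled to drink less. According to the Aim 2 text, all analyses are also repeated in three disease cohorts, so the same test would be run several times.

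**Working it through.** **No stated figure to reproduce.** The document gives no standard error, mean, SD or within-person correlation for drinking days. Its only intraclass correlation, 0.04, is for site-counsellor clustering in the PEth sample size and says nothing about days within a person. The size below therefore rests on an assumed rho, shown as a range.

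**Step 1: variance.** For 30 days with probability p and within-person correlation rho, the variance of the count is 30p(1−p)·[1 + (30−1)·rho]. The model uses 30p(1−p). The ratio of true to model SE is therefore sqrt(1 + 29·rho), and the actual two-sided type I error of a nominal 5% test is 2·[1 − Φ(1.96/ratio)].

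| rho (assumed) | 1 + 29·rho | SE ratio | Type I error |
|---|---|---|---|
| 0.05 | 2.45 | 1.57 | 21% |
| 0.1 | 3.9 | 1.97 | 32% |
| 0.2 | 6.8 | 2.61 | 45% |
| 0.3 | 9.7 | 3.11 | 53% |
| 0.5 | 15.5 | 3.94 | 62% |
| 1 (limit) | 30 | 5.48 | 72% |

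Ratios of exactly 2 and 4 need rho = 3/29 = 0.103 and 15/29 = 0.517.

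**Step 2: the same in days.** The binomial model implies an SD of sqrt(30p(1−p)): 1.6 days at p = 0.1, 2.2 at p = 0.2 and 2.5 at p = 0.3. The ratio is the real SD divided by this. Three assumed examples:

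- mean 3, SD 5: 5/1.64 = 3.04
- mean 5, SD 6: 6/2.04 = 2.94
- mean 10, SD 10: 10/2.58 = 3.87

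**Step 3: does the counsellor effect absorb the variation?** This was simulated under no arm effect with 405 participants (450 less 10%), p = 0.2, beta-binomial counts, 4 or 8 counsellors in all, and a binomial-logit model with a counsellor random intercept. There were 200 runs per setting. Site effects and covariates were left out, and the numbers of counsellors are assumptions.

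| Layout | rho | SE ratio (4 / 8 counsellors) | Type I error (4 / 8) |
|---|---|---|---|
| Crossed with arm | 0.1 | 1.91 / 2.16 | 33.5% / 35.5% |
| Crossed with arm | 0.3 | 3.47 / 3.26 | 58.5% / 63.0% |
| Crossed with arm | 0.5 | 4.23 / 3.70 | 68.5% / 60.5% |
| Nested in arm | 0.1 | 1.77 / 1.12 | 21.0% / 7.0% |
| Nested in arm | 0.3 | 1.75 / 1.41 | 29.5% / 19.0% |
| Nested in arm | 0.5 | 1.76 / 1.16 | 32.0% / 12.5% |

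When each counsellor has participants in both arms, the counsellor effect cancels from the comparison and the results follow the formula. When counsellors belong to one arm only, the counsellor variance takes up part of the person-level noise and the damage is smaller. With 200 runs, the standard error of a true 5% rate is sqrt(0.05·0.95/200) = 1.5 points, so the 7.0% entry alone is not clearly above 5%.

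**The case against.** **This could be detail left to an analysis plan.** That plan is not shown, and it could add a participant effect or a dispersion check without contradicting the article. This limits how serious the point is. It does not remove it, because the article names the distribution, the link and the random effects, and offers alternative models for another outcome only.

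**A reader might infer that the standard errors are two to four times too small as a matter of fact.** The documents do not support that. Rho is not given. The model is adjusted, so p varies with covariates and the residual rho is lower than the raw one. How counsellors relate to arm is not stated either. Counsellors take consent, enrol and assign, which suggests that they see both arms, but only the intervention arm receives counselling sessions. The lower range for nested counsellors therefore has to be reported beside the higher one.

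**A reader might extend the same factor to heavy drinking days.** The article does not state Binomial(30, p) for them. If they are reduced to a yes/no indicator, there is one value per person and the factor does not apply.

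**A reader might see this as a threat to the trial's main result,** because drinking days and heavy drinking days were the primary outcome before the change to PEth. They no longer are. The PEth analysis at 6 months uses one value per person. Nor are drinking days the only self-report result, since AUDIT is also a listed secondary outcome.

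**Conclusion.** The concern holds as a fault in a stated secondary analysis. As written, the model for drinking days omits person-to-person variation beyond the covariates and counts 30 correlated days as independent. The standard error is too small by about sqrt(1 + 29·rho). This is about 2 to 4 if the residual rho is 0.1 to 0.5 (type I error about 32% to 62%), and about 1.1 to 1.8 (type I error 7% to 32%) if counsellors are nested in arm. The direction is the same in every layout examined, but the size depends on a correlation and a counsellor layout that the document does not give. Heavy drinking days share the fault only if they are analysed as days out of 30. The primary PEth analysis is not affected.

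**What to change.** Name one of these for drinking days before the final analysis:

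- a participant-level random intercept added to the site and counsellor effects;
- a beta-binomial model that keeps the site and counsellor effects;
- a quasi-binomial or GEE model with participant-robust standard errors. Site and counsellor still have to be handled, because robustness at participant level does not cover clustering by counsellor.

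State whether the reported odds ratio is subject-specific (random intercept) or marginal over participants (beta-binomial, GEE), because the two differ in size. If many participants report zero days, a normal random intercept may fit poorly, so its fit should be checked or one of the other options chosen.

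State whether heavy drinking days are analysed as days out of 30 or as an indicator. If as days, use the same model.

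The cost is one or two sentences of analysis text and wider confidence intervals for this outcome. No new data, visits or participants are needed.
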